## Abstract

The ROBoCoP project is launched within the EU COST Action CA16113 “CliniMARK” aiming to increase the number of clinically validated biomarkers and focused on chronic obstructive pulmonary disease (COPD) biomarker development and validation. ROBoCoP encompasses two consecutive studies consisting of a pilot study followed by a field study. The pilot study is a longitudinal exposure assessment and biomarker study aiming at: 1-understanding the suitability of the candidate biomarkers in surveying populations at risk such as workers exposed to COPD causing agents; 2-determining the best sampling plan with respect to the half-life of the candidate biomarkers; 3-implementing and validating the sampling procedures and analytical methods; 4-selecting the best suitable biomarkers to be measured in the field. Each study participant is surveyed every day during the 6–8 h work-shifts for two consecutive weeks. The field study has an implementation research designe that enabled us to demonstrate the applicability of the standardized protocol for biomarker measurements in occupational settings while also assessing the biomarkers’ validity. ROBoCoP will focus on particulate matter (PM) exposure measurements, exposure biomarkers and a series of effect biomarkers, including markers of lipoperoxidation: 8-isoprostane, malondialdehyd in exhaled breath condensate (EBC) and urine, potential markers of nitrosative stress: NO_2_^−^, NO_3_^−^ and formate anion in EBC; markers of DNA oxidation: 8-hydroxy-2’deoxyguanosine in EBC and urine, marker of genotoxicity: micronuclei in buccal cells, and oxidative potential in exhaled air (OPEA). OPEA appears particularly promising as a clinical biomarker for detecting COPD, and will be tested independently and as part of a biomarker panel. COPD diagnosis will be performed by an experienced occupational physician according to international diagnostic standards and confirmed by a pulmonologist.

This research will include approximatively 300 underground subway workers randomly selected from the personnel registry of a large Parisian transport company. Underground subways are suggested as the most PM polluted urban transport environment. We believe this occupational exposure is relevant for biomonitoring of workers and early detection of respiratory diseases.

## Background

The ROBoCoP project was developed within the EU COST Action CA16113 “CliniMARK”, which aims to increase the number of clinically validated biomarkers (https://clinimark.eu/clinimark.html) and focused on chronic obstructive pulmonary disease (COPD) biomarker development and validation [1].

COPD is a major and increasing global health problem. It is the third leading cause of death [2], the second contributing disease of disability-adjusted life-years lost [3], and the most common cause of respiratory failure. In terms of cost, the annual burden of COPD is estimated to €38.7 billion in Europe, with up to 73% of the costs related to inability to work. COPD affects 334 million people in the world, with a global prevalence of 11.7% [4]. In Europe, the prevalence of COPD ranges between 13.5 and 13.9% and is twice for men compared to women [4].

Smoking is the main but not the only risk factor for the COPD development. Occupational exposures to dusts, vapours, gases, and fumes, exposure to indoor and outdoor air pollution, maternal smoking during pregnancy or early childhood, genetic and dietary factors were recently acknowledged as COPD risk factors [5, 6]. More than 20% of COPD cases are attributable to occupational exposure [6], while for non-smokers, the estimated attributable risk for COPD associated with occupational exposure is 31% [7]. One third of COPD patients exposed to fumes and dusts have to stop working definitively due to their respiratory problems [8].

Given that occupational but also environmental exposures to particulate matter (PM) trigger both development and exacerbation of COPD [9–12] and worsens its prognosis [8], both primary and secondary prevention are paramount. However, to make the latter effective, physicians have very little useful methods available to predict and detect early disease before it clinically appears. Spirometry is the most widely used method to diagnose COPD, although it is uninformative with respect to whether the disease is a new incident or has been present for many years. Moreover, only pre-bronchodilatation spirometry is often used in routine medical examinations, rising concerns of diagnostic misclassification [4, 13]. To monitor the development of disease, sequential measures of spirometry could be helpful but are not used routinely at present [13]. Biomarkers monitoring could help in identifying individuals with healthy lung function that will develop COPD is considered promising and encouraged with respect to the secondary prevention needs. Moreover, considering the poor screening performance of spirometry, the time it takes for one test (20–90 minutes) and consequently the cost, having easy to measure, diagnostic biomarkers at disposal would be more cost-effective from a public health perspective. It will allow screening populations at risk, such as occupationally exposed workers or people living in polluted environments and targeting preventive interventions.

PM is the most important component of air pollution, and is common in occupational exposure of transport workers. Transport is an important source of PM pollution. In many cities, subway PM concentrations far exceed WHO recommended limits for 24 h average particle exposure of 50 and 25 μg/m^3^ for PM10 and PM2.5, respectively, presenting a potential risk for regular passengers and subway workers [14, 15]. Moreover, subway PM have a very particular physical-chemical composition and size distribution. In contrast with outdoor PM, subway PM is highly ferruginous, with up to 67% iron oxide (Fe2O3) in the PM2.5 mass [16] and up to 50% in the PM10 [17] and contains trace metals along with organic aerosols and minerals. PMs induce their toxicity via inflammatory and oxidative stress pathways [18, 19]. The oxidative stress mechanism plays a central role in the pathophysiology of COPD [20–22], but also of other respiratory diseases. Oxidative stress is able to induce epigenetic changes as result of direct activation of oxidative stress response genes and inflammation as result of indirect intracellular signalling pathways, through the overproduction of reactive oxigen species  (ROS) and altered gene expressions. ROS induce the cellular release of inflammatory mediators, impairing phagocytosis of apoptotic cells and weakening the ability of corticosteroids to repress proinflammatory gene expressions [23]. Inflammation, lipid peroxidation, protein and DNA oxidation can result in tissue damage, protein alteration, modified gene expression, and remodeling of extracellular matrix and mucus. The biomarkers of these effects are therefore relevant candidates for further development [19]. A large majority of biomarkers has been measured in blood [22, 24, 25] and bronchoalveolar lavage fluid [26] which require invasive sampling procedures in hospital settings. In occupational and environmental settings, safe and easily obtained biological samples are necessary [27, 28], that is why ROBoCoP is focused on non-invasive biomarkers of oxidative stress, which might be measured in exhaled air or its condensate (EBC) and urine.

The determination of the oxidative potential in exhaled air (OPEA) appears to be a novel clinical biomarker and a promising approach for detecting COPD. The OPEA analyser (EU and US patent) [29], makes the OPEA measurements available in 3 minutes and can easily be used in occupational settings. Preliminary results showed that the OPEA measured for COPD patients is significantly higher than for controls [30]. Moreover, OPEA correlates significantly with the FEV1/FVC ratio [30]. However, to be fully characterized and validated, the OPEA analyser should be assessed in different situations, and on large samples of well characterized participants. Moreover, using it within a panel of oxidative stress biomarkers may be more efficient in diagnosing COPD than a single biomarker. For that purpose, ROBoCoP focuses on a series of biomarkers including: markers of lipoperoxidation: 8-isoprostane, malondialdehyde (MDA) in EBC and urine [31–33], markers of nitrosative stress: NO_2_^−^, NO_3_^−^ [32] and formate anion [34, 35] in EBC; markers of DNA oxidation: 8-hydroxy-2’deoxyguanosine in EBC or urine and OPEA.

For implementing this trial in the field, we chose an occupational setting of the Parisian transport company (45,000 active workers), and particularly its underground subway, as subway indoor air was reported the most PM polluted urban transport environment [36–40].

## Methods/Design

### Aims and Design of the Study

The project encompasses two consecutive studies consisting of a pilot study followed by a field study.

The pilot study is a longitudinal exposure assessment and biomarker study, serving as an orientation to the field study. This pilot study aims to: (1) understand the suitability of the candidate biomarkers in surveying populations at risk such as workers exposed to COPD causing agents; (2) determine the best sampling plan with respect to the half-life of the candidate biomarkers; (3) implement and validate the sampling procedures and analytical methods; (4) select the best suitable biomarkers to be measured in the field study. The pilot study is planned to follow each study participant daily during the work-shift for two consecutive weeks. The field study has an implementation research design. Within the context of field trials, implementation research focuses on “optimizing the delivery of existing interventions that have previously been shown to be efficacious when implemented well” [41]. In our context, the field study will enable us to demonstrate the applicability of the standardized protocol for biomarker measurements in occupational settings while assessing the biomarkers validity.

### Research Setting and Participants

The research will be conducted in a Parisian urban transport company in France for the experimental part and at Unisanté in Switzerland for the analytical part. The study samples will comprise three categories of underground subway workers: locomotive operators, security guards, and station agents in charge of information, ticket sale and control. All these professionals have their workstations underground. These jobs are considered the most exposed to PM compared to other professionals working outdoor, such as bus or tram drivers, controllers and administrative staff. They are also less concerned with other chemical exposure compared to maintenance workers.

The pilot longitudinal study will use a convenience sample of nine workers; three workers per occupation. Both women and men aged 40+, and non-smokers for at least 10 years (to avoid interference of smoking with the exposure-biomarkers-health outcome relationships) will be considered eligible. The only exclusion criteria are a counter-indication of spirometry test and acute or chronic morbidities other than COPD. The participants will have their workstations on subway line 7. This line is entirely underground, deep, has no mechanical ventilation and therefore represents one of the worst case scenarios in terms of exposure and one of the best for setting a pilot study. It offers a possibility to set up rooms for participant reception, biological sampling and equipment storage. The workers recruitment will be managed by the medical coordinator of the study. The medical coordinator will organise internal company meetings with workers, their supervisors and occupational physicians. At these meetings, workers will be informed on the objectives of the pilot study, inclusion criteria and invited to contact their occupational physician to declare their wish to participate in the study and to arrange an individual interview for this purpose. The occupational physicians will check the inclusion and exclusion criteria and collect the signed written informed consent form eligible workers. The recruitment of workers will be carried out in chronological order: The eligible workers who volunteer first will be given priority.

For the field study, we will include both male and female adults regardless their smoking status. The only exclusion criteria will be a counter-indication of spirometry test (e.g., recent surgery to the head, chest, stomach, or eye, unstable angina, excessive hypertension, or a recent myocardial or stroke). We will construct a probability sample maximizing the number of workers at risk with regard to the primary health outcome (COPD). For this, an automatic stratified randomization procedure will be applied on the register of 10,778 underground workers prepared by the company’s human resources department. The strata will be defined by four variables: sex, age, smoking status (smokers, ex-smokers, non-smokers) and exposure (depending on the occupation: station agents, security guards and locomotive operators). This sample will comprise approximatively 300 workers who would provide a signed written informed consent for participation, answer the epidemiological questionnaire and participated in the medical check and biological sample collection, as described further. The sample size was calculated assuming a 13.7% prevalence of COPD [4] and the statistical distribution of the OPEA values corresponding to the preliminary study conducted in a clinical setting [30]. The sample of 300 participants will allow discriminating with 90% power COPD cases from the controls with an area under the ROC curve of 0.64 or 0.70. These values correspond to an absolute or a relative difference between OPEA and the oxidative potential of the indoor air, respectively. If including 400 subjects, these will be respectively 0.66 and 0.72. Thus, we decided to limit our study to 300 participants. Assuming a participation refusal rate of 25%, a first sample of 400 workers will be contacted by their occupational physician. Eligible and voluntary workers, estimated to 300 participants approximatively, will be enrolled, after providing a written consent.

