The constraints of our pilot study protocol entailed a very intensive field data collection from no more than nine participants, with one physician, one nurse, two PhD students, and a support team of five technicians present in the companies over six weeks. Given the diversity of exposure metrics and measurements and devices available it was hardly possible to include more participants. This drawback of the very complete exposure assessment in the pilot study, will be compensated with a large probabilistic sample in the field study. The latter is expected to have 90% statistical power to discriminate COPD cases from controls based on a quite small OPEA difference. On the other hand, a possible lack of power induced by the relatively small number of workers included in the pilot study will be compensated for by the exposure variance when including both highly exposed and less exposed workers, such as locomotive operators and station agents, respectively. It is noteworthy that the repeated measure design (twenty measurements per participant for urine and EBC) will contribute to increase the power of detecting short-term effects.

Bacterial contamination and endotoxin measurements were not included in the protocol due to limited resources, but also because these exposures do not raise any particular concern at the company. However, the COVID-19 pandemic has strongly affected the working conditions of subway professionals and possibly the respiratory health of those who have contracted this disease. If the pandemic continues, then this situation is likely to be an issue for a timely start and progress with the field study. To guaranty the participant and staff safety, the planning and logistics of worker medical checks should be revised. This may delay the sample and data collection process, but also decrease the participation rate. Indeed, additional time, equipment and human resources will make the field study more expensive.

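### The field study's power statement is incoherent as written: the AUC attached to 90% power rises from 300 to 400 workers, and the choice of 300 is drawn from that comparison

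*Protocol article*

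**What the plan says.** All of this concerns the field study. In Research Setting and Participants, the Protocol article bases the calculation on two inputs: "The sample size was calculated assuming a 13.7% prevalence of COPD", and "the statistical distribution of the OPEA values corresponding to the preliminary study conducted in a clinical setting". It prints no means, standard deviations or AUC from that preliminary study.

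The result is then given: "The sample of 300 participants will allow discriminating with 90% power COPD cases from the controls with an area under the ROC curve of 0.64"; the same sentence adds 0.70 as an alternative. The two values belong to two versions of the marker: "These values correspond to an absolute or a relative difference between OPEA and the oxidative potential of the indoor air, respectively". The larger sample follows: "If including 400 subjects, these will be respectively 0.66 and 0.72". The decision comes next: "Thus, we decided to limit our study to 300 participants".

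The Discussion repeats the claim when it sets the large field sample against the small pilot: "The latter is expected to have 90% statistical power to discriminate COPD cases from controls based on a quite small OPEA difference".

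**The concern.** Two features of the four figures conflict with what a detectable AUC is.

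- **Direction.** At fixed power, alpha and prevalence, more workers make a smaller AUC detectable. The text has it rising by 0.02 for both indices, and the decision sentence follows directly from that comparison.
- **Two values at one sample size.** In a rank-based test against 0.5, the detectable AUC depends almost entirely on the numbers of cases and controls. Both OPEA indices are measured in the same workers, so it cannot be 0.64 for one and 0.70 for the other.

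This is the only power basis the article gives for the field study, and it is also the stated reason for the sample size. A reader cannot tell from it what size of effect the study is designed to find.

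**Working it through.** **Inputs.** From the article: prevalence 13.7%, N = 300 or 400, power 90%. Cases: 300 × 0.137 = 41.1, so 41 cases and 259 controls; 400 × 0.137 = 54.8, so 55 and 345. Assumed, because the article does not give them: alpha 5%, one- or two-sided, and a null AUC of 0.5.

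**Formula.** Hanley-McNeil variance of an AUC A with m cases and n controls:

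Var(A) = [A(1−A) + (m−1)(Q₁−A²) + (n−1)(Q₂−A²)] / (mn), where Q₁ = A/(2−A) and Q₂ = 2A²/(1+A).

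The AUC detectable against A₀ with 90% power solves A = A₀ + z·SE(A₀) + 1.282·SE(A), with z = 1.960 (two-sided) or 1.645 (one-sided).

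**Step 1: try to reproduce the printed figures as detectable AUCs against 0.5.**

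- N = 300, two-sided: 0.5 + 1.960 × 0.0486 + 1.282 × 0.0491 = 0.658.
- N = 400, two-sided: 0.5 + 1.960 × 0.0420 + 1.282 × 0.0427 = 0.637.

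| | N = 300 | N = 400 |
|---|---|---|
| Printed, absolute / relative index | 0.64 / 0.70 | 0.66 / 0.72 |
| Recomputed, two-sided 5% | 0.658 | 0.637 |
| Recomputed, one-sided 5% | 0.643 | 0.624 |

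Other variance formulas (Obuchowski binormal, exact binormal Mann-Whitney; null or alternative variance in the critical value) give 0.649-0.659 and 0.630-0.638 two-sided, and 0.636-0.644 and 0.618-0.625 one-sided. The direction is always downward. The spread between formulas is about 0.01, far below the 0.06 gap between the two indices. No single alpha gives 0.64 at 300 and 0.66 at 400.

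**Step 2: power at the printed AUCs with 300 workers.** Power = Φ{[A − 0.5 − z·SE(0.5)] / SE(A)}.

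- A = 0.64, two-sided: (0.14 − 0.0953)/0.0494 = 0.91, power 82% (81-86% across formulas).
- A = 0.64, one-sided: (0.14 − 0.0799)/0.0494 = 1.22, power 89% (88-92% across formulas).
- A = 0.70: 98.5% or more on every formula.

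**Step 3: try the printed figures as null AUCs to be excluded.** Setting A₀ to each printed value and solving for the true AUC (two-sided 5%):

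- Absolute index, N = 300: 0.64 + 1.960 × 0.0494 + 1.282 × 0.0435 = 0.792.
- Absolute index, N = 400: 0.66 + 1.960 × 0.0423 + 1.282 × 0.0376 = 0.791.
- Relative index, N = 300: 0.70 + 1.960 × 0.0480 + 1.282 × 0.0393 = 0.844.
- Relative index, N = 400: 0.72 + 1.960 × 0.0408 + 1.282 × 0.0340 = 0.844.

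One-sided 5% gives 0.778 and 0.779 for the absolute index, and 0.831 and 0.832 for the relative index. So a single true AUC per index fits each pair, and the rise from 300 to 400 is then in the right direction. The other variance formulas move the back-solved values (to about 0.76 and 0.81 at the lowest), but each pair still agrees to within 0.005.

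**The case against.** The strongest defence is Step 3: the authors may have computed sound figures and described them badly. That reading explains all four numbers. It also explains why a preliminary OPEA distribution was needed, since an expected AUC for each index requires one and a detectable AUC against 0.5 does not. On that reading 100 more workers raise the excluded bound by only 0.02, and stopping at 300 can be a sensible choice. This stands, and two stronger conclusions that a reader might draw do not.

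- **That 90% power is not delivered.** The 82% at AUC 0.64 needs a two-sided 5% test against 0.5, and the article states neither sidedness nor null value. One-sided, power is about 89%, close to the claim. AUC 0.70 is covered on any of these assumptions, so a shortfall could concern only the absolute index. The 41 cases are also a planning figure: the sample is meant to favour workers at risk, and about 56 cases in 300 would bring two-sided power at 0.64 to about 90%.
- **That the figures for 300 and 400 were swapped.** A swap fits 0.64 and 0.66 two-sided, but it cannot produce 0.70 and 0.72 in either order.

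The defence does not rescue the wording. The article names neither a null AUC nor an expected AUC, so the reader has no means of seeing that 0.64 might be a bound. The Discussion speaks of power for a small OPEA difference, which is the language of a detectable effect. A condensed article may leave alpha and sidedness to the full protocol, but the figures it does print must agree with one another.

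**Conclusion.** The concern holds as a defect of the power statement, not as a proven loss of power. Read as detectable AUCs, the figures contradict each other whatever alpha was used: the value must fall from 300 to 400 (by about 0.02 here), and one sample cannot have detectable values of both 0.64 and 0.70. Read as null bounds, they agree with each other, but the power then presumes a true AUC of about 0.78-0.79 or 0.83-0.84. These values are back-solved and appear nowhere in the article. On that reading the Discussion's claim of 90% power for a quite small OPEA difference is not supported. On the first reading the stated comparison cannot justify 300. On the second it can, but only with a reason that the article does not give.

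The sizes rest on 13.7% prevalence, 5% alpha and the Hanley-McNeil variance. The direction of the inconsistency rests on none of these.

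**What to change.** In Research Setting and Participants, state what the AUC values are, with the null AUC, the expected AUC for each OPEA index, alpha and sidedness. Then, depending on the answer:

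- **If they are detectable AUCs against 0.5:** replace all four with one value per sample size. At two-sided 5% these are about 0.66 for 300 workers (41 cases, 259 controls) and about 0.64 for 400 (55 and 345).
- **If they are null bounds to be excluded:** keep the numbers, label them as bounds, and print the expected AUCs on which the 90% depends.

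The recomputed values should not go in until the authors confirm which case applies; otherwise correct bounds could be overwritten by an unrelated calculation.

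In either case, give the actual reason for 300, such as feasibility or, if the values are bounds, a gain of only 0.02 for 100 more workers. Bring the Discussion sentence into line.

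The cost is rewording in two places. Enrolment and procedures do not change; the one drawback is that the stated figure may become less favourable.
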